### Design of the randomised evaluation

A cluster randomised trial (CRT) is being implemented in 60 rural communities with CBCCs supported by Save the Children’s ECD programme in Zomba district, Malawi. The evaluation follows a mixed-methods approach (combining quantitative and qualitative methods) with two rounds of surveys and assessments timed 1 year apart, including child, caregiver, household, CBCC and market-level data collection.

### Study site

The intervention is targeted to disadvantaged communities within Zomba district in Malawi. The proposed study population includes CBCCs currently supported by Save the Children with an ECD package, including parenting and CBCC quality improvement. The geographical area for intervention was targeted by Save the Children on the basis of a set of education variables that impact pupil attendance and achievement in school. Within Zomba, two traditional authorities (TAs) and two sub-TAs were selected based on need (education and health) and the presence of other NGOs to implement the ECD programme. Save the Children’s ECD programme currently reaches 228 communities, 109 in TA Chikowi, 42 in TA Mbiza, 37 in sub-TA (STA) Ntholowa and 40 in STA Ngwelero. Sixty-eight of these (27 in TA Chikowi and 41 in TA Mbiza) had benefited from the agricultural and nutritional components already and were, therefore, excluded from the evaluation.

### Study population

The evaluation targets all children aged 0–6 years in the 60 selected communities and their caregivers. The primary reference group for this study is children aged 3–6 years old living in the service area of a Save the Children‐supported CBCC. Secondary reference groups include their siblings and caregivers.

### Random assignment and manipulation of treatments

The 60 communities were randomly assigned to one of two treatment arms:Control group: communities with CBCCs supported by Save the Children’s ECD programme with no additional nutritional or agricultural supportIntervention group: communities with CBCCs supported by Save the Children’s ECD programme with additional nutritional and agricultural support

The integrated intervention package will be implemented in 30 of the 60 rural communities after the baseline survey and extended to the control communities after the end-line survey. There are several reasons why the control group in this case is not a control without intervention. The Government of Malawi is committed to scaling-up the ECD quality improvement across all CBCCs and an impact evaluation on the cost-effectiveness of different ECD quality improvement strategies is underway.^2^ The proposed evaluation complements the ongoing work by examining the relative impact and costs of alternative implementation models, focussing on how to enhance participation in the CBCCs and, at the same time, supporting the nutrition of children at a critical age in their development.

The 60 CBCCs were randomly selected in two stages from a pool of 235 CBCCs in 47 clusters currently assisted by Save the Children in Zomba. Due to the clustering of the CBCCs around primary schools, the list of 235 CBCCs was screened to flag clusters where more than one CBCC was being assisted. Twenty-six clusters were excluded from the first stage of randomisation to minimise possible contamination. An additional 10 CBCCs were dropped as they had ongoing activities. The 20 clusters were then randomly assigned to two groups of 10 clusters, where the randomisation was stratified geographically by traditional authority areas. In the second stage of randomisation, within each cluster, three CBCCs were then selected at random for the study. As six clusters had fewer than three CBCCs available for the study, in order to select a full sample of 30 CBCCs per treatment arm, additional CBCCs were randomly selected from three clusters (Gologota, St. Pius and Machereni).

### Sample sizes

Initial power calculations and resource availability had suggested the adoption of a sample with 30 clusters (communities) per treatment arm with 20 households in each cluster to identify reasonable treatment impacts of the intervention on the primary study outcomes. Data for power calculations was obtained from the 2010 Demographic and Health Survey (DHS) survey. We calculated means, standard deviations and intracluster correlation coefficients (ICCs) for rural children in Malawi. For Dietary Diversity Score (DDS), the mean and standard deviation for rural children aged 0–5 years were estimated to be 2.5 and 1.03, respectively. The ICC was 0.01. Plots of the standardised minimum detectable effect size (MDES) against the number of clusters assuming a sample of 25 children measured in each community (cluster size), consistent with 20 household interviews per community and considering that several children may end up not being tested, showed that only a marginal gain can be obtained by expanding the sample beyond 20 as power is mainly driven by the number of clusters [21] (see Fig. 2 for example simulations of MDES versus number of clusters with high and low ICCs).

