### Main hypotheses and outcome indicators

The expected impact of the intervention discussed in the analysis of the programme theory is summarised below. The intervention is expected to have a positive impact on:Preschool enrolment and attendanceChildren’s diets and household diet diversityInfant and young children’s nutritional status and childcare practicesAgricultural production

A limited impact is expected on:Micronutrient status, child development, physical growthAgricultural income

The main indicators for the evaluation are summarised in Table 2.

**Table 2 Tab2:** Main outcome indicators of the intervention

Type	Domain	Indicators
Primary	Diets	Individual intake and diet diversity score (children 36–72 m)
Primary	Childcare practices	WHO IYCF practices
Primary	CBCC participation	CBCC enrolment and attendance (children 36–72 m)
Primary	Agriculture	Production output, crop-mix
Secondary	Health and nutritional status	Anthropometry (weight-for-age, height-for-age, weight-for- age z-scores and MUAC) (children 6–72 m)
Secondary	Child development	Malawi Development Assessment Tool z-scores (fine motor, gross motor, language and social domains) (children 36–72 m)
Secondary	Gender	Women’s asset ownership, time use and productivity
Process	Meal service	Quality of CBCC meals, portion sizes, frequency

*CBCC* community-based childcare centres, *IYCF* Infant and Young Child Feeding, *MUAC* mid-upper arm circumference, *WHO* World Health Organization

Note that in addition to outcome indicators we will also observe the programme impact on intermediate indicators, particularly for those outcomes that are more difficult to observe directly. In the agricultural domain, we will look at intermediate outcomes such as input use (labour, land, seeds and fertiliser), investments (farm capital, such as tools and machinery) and market access (marketed surplus, prices and markets). The quantity, quality and timely preparation and delivery of food in the CBCCs will also be explored.

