**Fig. 3 Fig3:**
[figure not shown]
Impact pathways for the intervention on child nutrition and development (Fig. 3). (Source: adapted from [28])

After preliminary design visits to the targeted communities, the sampling strategy was modified to account for the implementation approach adopted by Save the Children, involving the clustering of CBCCs around surrounding primary schools. As a result, the cluster, or unit of randomisation was the primary school cluster that included a number of different CBCCs, rather than the CBCC itself. Adjusting for ICCs at the primary school cluster level, where 60 CBCCs were clustered into two groups of 15 primary school clusters, would provide 80% power to detect a 0.24-SD difference between treatment groups at the 5% level of significance (Table 3).

**Table 3 Tab3:** Sample sizes

	Primary clusters	Communities/CBBCs	Households with children of target age	Children (0–5 y)	Children (3–5 y)
Control	15	30	600	936	648
Intervention	15	30	600	936	648
Total	30	60	1200	1872	1296

Note: Number of children estimated based on demographic data from the Demographic and Health Survey (DHS), 2010

*CBBCs* community-based childcare centres

The sampling of households was conducted through a census within a certain catchment area for each CBCC including information on the target age groups living within each household. Households with children aged 3–5 years were then randomly selected for participation in the survey.

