	Non-food expenditures	Expenditures on household items, clothing and personal expenditures over the last month
Caregiver	Caregiver’s health and hygiene	Health- and hygiene-related questions
	Caregiver’s health and nutrition knowledge	Knowledge related to optimal infant and young childcare and feeding practices
	Caregivers IYCF practices	Infant and child feeding practices
	Childcare practices	Childcare practices, including support for learning and stimulation
	Women’s time allocation	Women’s use of time, perceptions on women’s time use
Child	Child health	Child immunisation history and health-related questions
	Dietary assessment	Interactive 24-h recall on food intake for children aged 3–5 years
	Anthropometry	Physical measurements of all children and their parents
	Development	MDAT scores (fine and gross motor, language and social domains)

*CBCC* community-based childcare centre, *IYCF* Infant and Young Child Feeding, *MDAT* Malawi Development Assessment Tool

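### The power paragraph does not match the design for the diet primary outcome: too few children aged 3–5 per community, a 0.24 SD that the visible text cannot reproduce, and 15 school clusters per arm where the randomisation section has 10

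*Protocol article*

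**What the plan says.** The Sample sizes section of the protocol article describes two stages of planning.

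- **Initial stage.** There are 30 communities per arm and 20 households in each, with plots drawn "assuming a sample of 25 children measured in each community (cluster size"). That number already allows for some children not being tested. The inputs come from a 2010 national survey. For the diet diversity score (DDS), "the mean and standard deviation for rural children aged 0–5 years were estimated to be 2.5 and 1.03", and then "The ICC was 0.01".
- **Final stage.** The unit of randomisation became the primary school cluster. With 15 such clusters per arm, and after adjustment for school-level ICCs whose value the text does not give, the design "would provide 80% power to detect a 0.24-SD difference between treatment groups at the 5% level of significance". Table 3 lists, per arm, 15 primary clusters, 30 communities, 936 children aged 0–5 and 648 aged 3–5.

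The diet primary outcome covers a narrower age group. Table 2 defines it as "Individual intake and diet diversity score (children 36–72 m"), and Table 4 describes the dietary module as "Interactive 24-h recall on food intake for children aged 3–5 years".

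The section on random assignment gives a different cluster count: 20 school clusters, randomised as two groups of 10, with three communities taken from each where available.

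**The concern.** Three parts of the power statement do not fit the design that it supports.

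1. The cluster size in the initial plots is larger than the number of children on whom the diet outcome can be measured.
2. The published inputs and the published result do not connect.
3. The result assumes more randomised units per arm than the randomisation section reports.

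This is the article's only power statement. If the diet result is null, a reader will use 0.24 SD to judge which effects have been excluded. That use is unsafe if the figure belongs to another cluster count, or to an ICC that the reader cannot see.

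**Working it through.** **Inputs.** Power is 80% and alpha 5%, taken as two-sided because sidedness is not stated. ICC is 0.01. Table 3 gives 15 clusters per arm and the random assignment section gives 10. Child counts are from Table 3.

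**Children per community.** Ages 3–5: 648/30 = 21.6. Ages 0–5: 936/30 = 31.2. The planned 25 exceeds every available child aged 3–5 before any loss. It is close to 31.2 × 0.8 = 24.96, which would fit the 0–5 group less about 20% untested.

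**Children aged 3–5 per school cluster.** 15 clusters per arm means two communities each: 2 × 21.6 = 43.2 (or 2 × 25 = 50 on the planning number). 10 clusters per arm means three each on average: 3 × 21.6 = 64.8.

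**Formula.** With k clusters per arm and m children per cluster,

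MDES = M × √(2[1 + (m − 1)·ICC] / (k·m)).

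M is 1.960 + 0.842 = 2.802 with normal quantiles. With t quantiles on 2k − 2 df it is 2.903 for k = 15 and 2.963 for k = 10. Equal cluster sizes and no baseline adjustment are assumed.

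**Attempt to reproduce 0.24 SD (k = 15, ICC 0.01).**

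- m = 50: √(2 × 1.49/750) = 0.0630, so MDES = 0.177 (normal) or 0.183 (t).
- m = 43.2: √(2 × 1.422/648) = 0.0662, so MDES = 0.186 (normal) or 0.192 (t).

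Neither gives 0.24.

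**ICC needed for 0.24 SD (k = 15).**

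| m | normal | t |
|---|---|---|
| 50 | 0.036 | 0.032 |
| 43.2 | 0.033 | 0.029 |

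There is one other route. ICC 0.01 with only 25 children in a whole school cluster gives 0.228 (normal) or 0.236 (t), and the latter rounds to 0.24. That contradicts Table 3, which puts two communities in each school cluster.

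**Effect of the age-group shortfall alone.**

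- Initial design (k = 30, ICC 0.01, t): 25 children gives 0.164 and 21.6 gives 0.174.
- Final design (k = 15), holding the ICC that gives 0.24 at m = 50: moving to m = 43.2 gives 0.247.

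The change is 0.01 SD or less.

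**Effect of 10 clusters per arm (m = 64.8), at each ICC implied by 0.24 SD.**

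| ICC implied by | normal | t |
|---|---|---|
| m = 50 | 0.282 | 0.287 |
| m = 43.2 | 0.273 | 0.277 |

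**Range over ICC (t quantiles, ages 3–5, no losses).**

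| ICC | k = 15, m = 43.2 | k = 10, m = 64.8 |
|---|---|---|
| 0.01 | 0.192 | 0.211 |
| 0.02 | 0.219 | 0.248 |
| 0.03 | 0.243 | 0.281 |
| 0.04 | 0.264 | 0.310 |
| 0.05 | 0.284 | 0.337 |

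**The case against.** The strongest reply is that the two stages are separate calculations. The 25 children and the ICC of 0.01 belong to the initial stage. The 0.24 SD belongs to the revised stage and is attributed to school-level ICCs. A reader might infer that the protocol derives 0.24 from 0.01 and gets the sum wrong, but the document does not say so. The final figure may also already use ages 3–5: 43.2 children per cluster with an ICC of about 0.03 gives 0.24. The ICC used may be printed in Fig. 2, which shows high and low ICC scenarios but is not visible here. All of this stands, and it limits the point on 0.24 SD to non-reproducibility from the visible text.

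Four further limits also stand.

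- No age is attached to the 25 children. That they are aged 0–5 is an inference from the arithmetic, and the age basis of the ICC comes only from context.
- The mean and SD do not enter a standardised detectable difference. They matter only if 0.24 SD is converted to food groups.
- The protocol itself says that going beyond 20 per community gains little, and 21.6 is above 20.
- If an ICC of 0.01 held at school level, the sample aged 3–5 would detect less than 0.24 SD even with 10 clusters per arm (0.199–0.211).

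The reply leaves two facts untouched. Twenty-five measured children per community is not attainable on average for the diet outcome. And the 0.24 SD is stated for 15 clusters per arm, while the article's own account of the randomisation has 10.

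**Conclusion.** The point holds as a mismatch between the power paragraph and the design, and it should be corrected.

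- **Cluster size.** The initial plots use 25 children per community where Table 3 supplies 21.6 of the measured ages. The consequence is small, about 0.01 SD.
- **Reproducibility.** With Table 3's design, the only ICC in the visible text gives about 0.18–0.19 SD. A figure of 0.24 needs a school-level ICC of about 0.03 that the text does not state, or a cluster size that contradicts Table 3.
- **Cluster count.** This is the material part. At the ICC implied by 0.24, 10 clusters per arm give about 0.27–0.29 SD, roughly 14–20% above the stated figure (0.273/0.24 = 1.14; 0.287/0.24 = 1.20).

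A reader might go further and conclude that the trial is underpowered for diet because of the age restriction. The documents do not support that: the age effect is minor, and the true school-level ICC is unknown.

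The sizes assume a two-sided test, equal clusters, no losses and no baseline adjustment. The 0.27–0.29 SD also assumes that the ICC behind 0.24 was applied with 15 clusters of 43.2 to 50 children.

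**What to change.** 1. Reconcile the random assignment section with the Sample sizes section and Table 3 on the number of school clusters randomised per arm.
2. State the school-level ICC and the number of children per school cluster behind 0.24 SD.
3. Recompute the detectable difference for ages 3–5, using 21.6 children per community less the expected untested share and the number of clusters actually randomised. Restate 0.24 SD accordingly.
4. Say that the DDS mean and SD come from ages 0–5. Where the survey allows, re-derive them and the ICC for children aged 36 months and over. If no age-specific ICC can be obtained, show the detectable difference over ICC 0.01–0.05, as in the last table of the working.

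The cost is one recalculation and a corrected paragraph and table. No extra enrolment or change of design is needed. If 10 clusters per arm is confirmed and the ICC is near 0.03, the stated detectable difference becomes less favourable.

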**Fig. 2 Fig2:**
[figure not shown]
Diet diversity: minimum detectable effect size versus number of clusters, simulations with high and low intracluster correlation coefficients (ICCs)

**Fig. 3 Fig3:**
[figure not shown]
Impact pathways for the intervention on child nutrition and development (Fig. 3). (Source: adapted from [28])

After preliminary design visits to the targeted communities, the sampling strategy was modified to account for the implementation approach adopted by Save the Children, involving the clustering of CBCCs around surrounding primary schools. As a result, the cluster, or unit of randomisation was the primary school cluster that included a number of different CBCCs, rather than the CBCC itself. Adjusting for ICCs at the primary school cluster level, where 60 CBCCs were clustered into two groups of 15 primary school clusters, would provide 80% power to detect a 0.24-SD difference between treatment groups at the 5% level of significance (Table 3).

**Table 3 Tab3:** Sample sizes

	Primary clusters	Communities/CBBCs	Households with children of target age	Children (0–5 y)	Children (3–5 y)
Control	15	30	600	936	648
Intervention	15	30	600	936	648
Total	30	60	1200	1872	1296

Note: Number of children estimated based on demographic data from the Demographic and Health Survey (DHS), 2010

*CBBCs* community-based childcare centres

The sampling of households was conducted through a census within a certain catchment area for each CBCC including information on the target age groups living within each household. Households with children aged 3–5 years were then randomly selected for participation in the survey.

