### Trial status

The first participant was enrolled on 7 September 2015. Data collection for the last of 120 participants will be completed by December 2016 (see the SPIRIT Checklist figure (Additional files 1 and 2)) (Fig. 4).

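### The 80% power for 0.24 SD is calculated for 15 randomised primary-school clusters per arm, but the allocation section reports 10 per arm

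*Protocol article*

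**What the plan says.** In Methods, Sample sizes, the article explains that after design visits the sampling strategy was changed because CBCCs are grouped around primary schools. It then says that "the cluster, or unit of randomisation was the primary school cluster that included a number of different CBCCs, rather than the CBCC itself". The power statement, which uses a 5% significance level, follows: "60 CBCCs were clustered into two groups of 15 primary school clusters, would provide 80% power to detect a 0.24-SD difference between treatment groups". Table 3 gives the same layout: 15 primary clusters, 30 communities, 600 households and 648 children aged 3–5 years in each arm, so 30 clusters in total.

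Under Random assignment and manipulation of treatments, the article describes the allocation as carried out: "The 20 clusters were then randomly assigned to two groups of 10 clusters", stratified by traditional authority area. Three CBCCs were then drawn per cluster. It adds: "As six clusters had fewer than three CBCCs available for the study", and says that extra CBCCs were taken from three clusters to reach 30 per arm. The same section opens with "The 60 communities were randomly assigned to one of two treatment arms", which is loose wording, since the two-stage procedure set out below it randomises school clusters.

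The power statement refers to ICCs at primary-school-cluster level without giving a value.

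**The concern.** Both sections give 60 CBCCs, 30 per arm. They disagree only on the number of randomised units, 30 or 20, and in a cluster-randomised trial that number largely fixes the power. The Sample sizes section itself says that power depends mainly on the number of clusters.

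The 15-per-arm calculation is also not a leftover from before the redesign. It is presented as the revised calculation that takes school clustering into account. If the allocation section is right, the stated detectable difference belongs to a design that was not randomised, and a reader would take the trial to be more sensitive than it is. Table 3 would also overstate the number of independent units by half.

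**Working it through.** **Inputs.** 648 children aged 3–5 per arm (Table 3); 15 clusters per arm (Sample sizes, Table 3) or 10 (allocation section); 0.24 SD, 80% power, 5% level (Sample sizes). Assumptions: two-sided test, equal cluster sizes, all clustering at school level, no baseline adjustment. The school-level ICC is unknown.

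**Formulas.** With k clusters per arm, N children per arm and m = N/k:
- design effect DE = 1 + (m − 1) × ICC
- standard error of the difference, in SD units, SE = √(2 × DE / N)
- power from a noncentral t with 2k − 2 df and noncentrality 0.24/SE; the minimum detectable effect (MDES) is the difference at which power is 80%.

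**Direction.** For fixed N and any ICC above zero, going from k = 15 to k = 10 raises m from 43.2 to 64.8. DE and SE rise and the df fall from 28 to 18, so power must fall. No ICC value is needed for this.

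**Step 1: the stated figure.** It cannot be reproduced directly without the ICC, so I solved for the ICC that yields it. With k = 15, an ICC of 0.0288 gives DE = 1 + 42.2 × 0.0288 = 2.215 and SE = √(2 × 2.215/648) = 0.0827. The multiplier for 80% power at 28 df is 2.902, and 2.902 × 0.0827 = 0.240.

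**Step 2: the same ICC and children with 10 per arm.** DE = 1 + 63.8 × 0.0288 = 2.837 and SE = √(2 × 2.837/648) = 0.0936. The multiplier at 18 df is 2.963, so MDES = 2.963 × 0.0936 = 0.277 SD. At 0.24 SD the noncentrality is 0.24/0.0936 = 2.56 against a critical t of 2.10, and power is 68%.

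**Step 3: sensitivity to the inputs.** Each row back-solves the ICC from 0.24 SD at 15 per arm, then sets k = 10.

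| Assumption | Implied ICC | Power at 0.24 SD | MDES (SD) |
|---|---|---|---|
| 648 per arm, t | 0.029 | 68% | 0.277 |
| 648 per arm, normal | 0.033 | 69% | 0.273 |
| 600 per arm, t | 0.027 | 69% | 0.275 |
| 750 per arm, t | 0.032 | 67% | 0.281 |
| 936 per arm, t | 0.036 | 66% | 0.285 |

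**Step 4: where the clustering sits.** The number of CBCCs stays at 30 per arm, so clustering at CBCC level is unaffected by the change from 15 to 10. With SE² = 2 × (school ICC/k + CBCC ICC/30 + remainder/648), re-solved to 0.24 SD at 15 per arm:
- half the clustering at CBCC level: power 71%, MDES 0.267 SD
- three quarters at CBCC level: power 74%, MDES 0.259 SD.

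**Step 5: unequal clusters.** The article does not give CBCC counts per cluster, so these layouts are illustrations. Both total 60 CBCCs over 20 clusters, with 21.6 children per CBCC (648/30), ICC 0.029 and each cluster weighted by m/DE:
- 11×3 + 3×5 + 6×2: power 67%, MDES 0.28 SD
- 11×3 + 3×7 + 6×1: power 64%, MDES 0.29 SD.

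**Step 6: when the claim would survive.** With 10 equal clusters per arm, 648 children, and all clustering at school level, power at 0.24 SD by ICC (t-based) is 89% at 0.01, 77% at 0.02, 67% at 0.03, 52% at 0.05 and 33% at 0.10. It reaches 80% only when the ICC is below about 0.018.

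**The case against.** The strongest reply is that the school-level ICC is unreported and the loss is back-solved. At an ICC of 0.01 the 10-per-arm design would still have about 89% power, and 15 per arm might yet be the true count. This stands as a limit on the size of the loss. It does not remove the contradiction: at an ICC low enough for 10 per arm to keep 80% power, 15 per arm would detect less than 0.24 SD, so the published figure would still not describe the 10-per-arm design. The planned ANCOVA on baseline could also recover some power, but the power statement takes no credit for it.

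Several stronger readings are tempting and are not supported:

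- A reader might infer that 0.24 SD is an arithmetic error because "The ICC was 0.01", which gives about 0.19 SD at 15 per arm. But that ICC belongs to the initial calculation with communities as clusters. The 0.24 SD is said to use school-level ICCs, and a condensed article may leave that value out.
- A reader might count 47 clusters less 26 excluded as 21, not 20. The next sentence drops a further 10 CBCCs, which could have removed one cluster.
- A reader might put the loss as far as 0.31 SD and 58% power for uneven clusters. That requires all six short clusters to have exactly one CBCC and an inflation that is conservative for the planned multilevel models. With efficient weighting, the same layout gives 0.29 SD and 64%.
- "Data collection for the last of 120 participants will be completed by December 2016" conflicts with 1200 households in Table 3, but it has no bearing on power.

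Nor does the discrepancy invalidate the analysis. The multilevel models and clustered standard errors do not take their cluster count from Table 3, and a null result would be judged by its confidence interval.

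**Conclusion.** The point holds. The article gives two incompatible counts of randomised clusters, and its 80% power for 0.24 SD rests on the larger one. If 10 per arm were randomised, as the allocation section reports, power is lower than stated for any positive school-level ICC at the same number of children. That direction is certain.

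The size is an inference. On the ICC implied by the article's own figure, power at 0.24 SD is about 68% and the MDES about 0.28 SD. It is about 71–74% and 0.26–0.27 SD if half to three quarters of the clustering is at CBCC level, and roughly 64–67% and 0.28–0.29 SD under the illustrative unequal layouts. This is a moderate loss. A reader might conclude outright that the trial is underpowered. The documents do not show that, because the school-level ICC is not given and they do not settle which count is correct.

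**What to change.** Establish from the allocation records how many primary-school clusters were randomised, and give that one count in the allocation section, the power statement and Table 3.

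- **If 10 per arm:** change Table 3 to 10 + 10 = 20 and replace the 0.24 SD statement with the MDES, or the power at 0.24 SD, for 10 per arm. State the school-level ICC used, take 18 df and the actual CBCC counts per cluster, and show a small range of ICCs. Baseline data can supply the estimate.
- **If 15 per arm:** correct the allocation section and leave Table 3 as it is. The school-level ICC should still be stated.

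In either case, reword the sentence about 60 communities being randomly assigned so that the school cluster is named as the randomised unit.

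The cost is rewording and one recalculation, with no extra participants or data collection. If 10 per arm is correct, the published detectable effect will probably become less favourable than 0.24 SD.
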